### Statistical Methods

All participants will be included in an intention-to-treat analysis. Continuous outcomes will be examined using linear mixed-effects models with random intercepts accounting for repeated measures and missing data. The models will include terms for treatment group, time (modeled as a continuous variable), and the treatment-by-time interaction to estimate differential change between groups. An autoregressive covariance structure will be applied to account for temporal correlation. Statistical significance will be defined as a 2-sided *P* value of less than .05. Between-group effect sizes will be estimated using the Cohen *d*. All analyses will be conducted using RStudio (Posit PBC).

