**Primary**					
	Inattention symptoms	SNAP-IV^a^ inattention subscale (parent report)		Change (Δ) in total inattention score (range 0-27)	
	Inhibitory control	Go/no-go task (computerized)		Number of commission errors (responses to “no-go” stimuli); age corrected	

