#### Primary Outcomes

Primary outcomes comprise (1) inattention symptoms (assessed via the Swanson, Nolan, and Pelham Rating Scale version IV inattention subscale [parent report]), for which the primary metric is the change in the total inattention score [14]; and (2) inhibitory control (measured via a computerized go/no-go task [15]), for which the primary metric is the number of commission errors (responses to “no-go” stimuli), representing a failure in inhibitory control.

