### Sample Size

The sample size calculation assumed a statistical power of 0.80, a significance level of an α value of .05, and a medium effect size of 0.50, consistent with literature on exercise interventions in ADHD. Accounting for an expected attrition rate of 30%, the required total sample size is 98 participants, with 49 participants allocated to each study arm. We will balance recruitment across the 2 study sites.

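### The primary mixed model leaves baseline means free by arm, so it tests an essentially unadjusted difference in change: valid, but less precise than a baseline-adjusted analysis of the same data

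*Protocol article*

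**What the plan says.** Statistical Methods in the protocol article gives the model for continuous outcomes: a linear mixed model with random intercepts and an autoregressive covariance. Its fixed effects are stated as: "The models will include terms for treatment group, time (modeled as a continuous variable), and the treatment-by-time interaction". The interaction is there to capture how the arms differ in change. No baseline covariate and no common-baseline constraint is named. Testing is at the 5% level: "Statistical significance will be defined as a 2-sided" *P* value below .05.

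The Outcomes overview gives two assessments, visit 1 and visit 5. For SNAP-IV inattention, Primary Outcomes describes the measure as one "for which the primary metric is the change in the total inattention score". For go/no-go, the metric is the number of commission errors.

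Sample Size reads: "The sample size calculation assumed a statistical power of 0.80", with "a significance level of an α value of .05" and "a medium effect size of 0.50, consistent with literature on exercise interventions in ADHD". It allows for 30% attrition and arrives at 98 participants, 49 per arm.

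**The concern.** Randomisation makes the arms equal at baseline in expectation. A model with a free group term does not use that fact: it estimates a separate baseline mean for each arm and subtracts it. The noise in those two baseline means then enters the treatment estimate. A model that adjusts for baseline, or constrains the two baseline means to be equal, removes that noise using measurements the trial already takes.

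Precision is scarce here. If attrition runs as planned, about 34 participants per arm will have a visit-5 score, and each primary outcome rests on a single between-arm contrast.

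**Working it through.** **Inputs from the protocol article.** Two visits; 49 per arm; 30% attrition, so a fraction f = 0.7 observed at visit 5 (49 × 0.7 = 34.3, taken as 34); two-sided 5% level; effect size 0.50.

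**Assumptions.** The pre-post correlation r is not given, so a range is shown. SDs are equal at both visits and set to 1. The effect of 0.50 is read in raw-score SD units, since Sample Size does not say whether it refers to the score or to change. Visit-5 scores are missing at random. Normal theory is only an approximation for the commission-error count.

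**The plan's own figure.** A two-sided two-sample comparison at d = 0.50 and 80% power needs 63 per arm (normal) or 64 (t). After division by 0.7 this is 90 or 92 per arm, 180 or 184 in total, so 98 is not reproduced. Under that simple formula, power is 70% with 49 per arm and 54% with 34. This is a separate matter, but it shows how little precision there is to spare.

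**Step 1: what the interaction estimates.** With complete data and visits coded 0/1, it equals the difference in mean change. In simulated complete-data trials, the fitted interaction and that difference agreed to about 1e-15.

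**Step 2: complete data.** Per-participant variance is 2(1-r) for change and 1-r² after baseline adjustment. The ratio is (1+r)/2, so the information lost is (1-r)/2. At r = 0.5 this is 0.5/2 = 25%.

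**Step 3: planned attrition, all baselines kept.** In each arm the stated model estimates mean change as (observed visit-5 mean) - r × (baseline mean of those observed) - (1-r) × (baseline mean of all randomised). Its per-participant variance is (1-r²)/f + (1-r)². With a common baseline mean the last term cancels between arms, leaving (1-r²)/f. The loss is (1-r)f / [(1+r) + (1-r)f]. At r = 0.5: 0.35/(1.5 + 0.35) = 19%.

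**Step 4: power.** For the stated model, Φ(0.5/√(2V/49) - 1.96) with V from step 3. At r = 0.5, V = 0.75/0.7 + 0.25 = 1.321, the standard error is 0.232, and Φ(2.153 - 1.96) = 58%. For the adjusted model, the standard error is √(2 × 0.75/34) = 0.210, and Φ(2.381 - 1.96) = 66%.

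| r | Loss, complete data | Loss, 30% missing | Power, stated model | Power, adjusted |
|---|---|---|---|---|
| 0.3 | 35% | 27% | 46% | 58% |
| 0.5 | 25% | 19% | 58% | 66% |
| 0.7 | 15% | 11% | 78% | 82% |
| 0.8 | 10% | 7% | 91% | 93% |

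A simulation of 600 trials per setting gave losses of 22% (complete) and 16% (30% missing) at r = 0.5, and 13% and 9% at r = 0.7, close to the formulas.

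**Step 5: chance imbalance.** A baseline difference D between the randomised arms shifts the estimate by -(1-r)D. With 49 per arm, D has SD √(2/49) = 0.20. At r = 0.5 a one-SD imbalance therefore moves the estimate by 0.5 × 0.20 = 0.10 SD, a fifth of the assumed effect.

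**Step 6: can adjustment alone reach 80%?** It needs 34 = (1.96 + 0.842)² × 2(1-r²)/0.25, that is 34 = 62.8(1-r²). This gives r = √(1 - 0.5415) ≈ 0.68.

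**The case against.** **The size is not in the documents.** Correct. A reader might take the loss to be about a quarter, but that needs r = 0.5, complete data and equal SDs together. The article supplies none of these, and it plans for 30% attrition.

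**Equal SDs may fail.** SNAP-IV entry requires a score of at least 12 on a 0-27 scale, which may narrow the baseline spread. With k the ratio of baseline to post SD, the complete-data variance ratio is (1-r²)/(1 + k² - 2rk). For illustration, k = 0.75 and r = 0.5 give 0.75/0.8125, a loss of only 8%. This stands as a caution on size but not on direction: the denominator exceeds the numerator by (k-r)², which is never negative.

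**The stated model uses baseline-only participants.** It does, and the comparison must credit it for them. With complete pairs only, its power at r = 0.5 would look like 54%; with all 49 baselines per arm it is 58%. The figures above are on that fairer basis.

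**The model is unbiased.** It is, over randomisation. A reader might infer that baseline imbalance passes into the estimate one for one. It does not: the factor is (1-r).

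**The outcome table does not conflict with the model.** A reader might infer that a change score cannot be the response in a model with a time term. Nothing says it is the response. Scores are modelled and change is the contrast, so the outcome definitions and the model agree.

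**An analysis plan may add covariates.** The list of terms need not be exhaustive, and the dataset stays locked until the analysis plan is final. That leaves room to make the improvement, but the model as the article fixes it has a free group term.

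**Conclusion.** The point holds as one of efficiency. The stated model is valid, but for the same data it is no more precise than a baseline-adjusted analysis at any r, and with equal SDs it is strictly less precise at every r below 1. The loss is about 7-27% of the information at the planned attrition and 10-35% with complete data, for r from 0.8 to 0.3. In power terms, adjustment gains about 12 points at r = 0.3, 8 at 0.5 and 4 at 0.7.

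These sizes rest on an assumed r, equal SDs, an effect expressed in raw-score SDs, and normal theory for a count. A reader might hope that adjustment repairs the trial's power. It does not, unless r is about 0.68 or higher. The mismatch between 98 and a two-arm calculation needs its own answer.

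**What to change.** For both primary outcomes, keep the two-visit mixed model but constrain the baseline mean to be common to the arms. Use visit and visit-by-arm as fixed effects, site (the stratification factor) as a covariate, and an unstructured covariance. The visit-5 arm contrast is then the treatment effect, on the same scale as a difference in change. The unstructured covariance lets the two SDs differ, so the analysis does not depend on the equal-SD assumption used above. Baseline-only participants stay in, as the intention-to-treat statement requires.

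ANCOVA of the visit-5 score on arm, baseline and site can serve as a supporting analysis. It should not be the primary one, because it drops participants without a visit-5 score.

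The cost is wording in the protocol or analysis plan. If the protocol is amended, its own rule on ethics submission and registry update applies. No interim analysis has been done and the analyst is blinded, so the change can be made and dated before any comparative result is seen.

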### Outcomes

#### Overview

We will assess outcomes at baseline (visit 1) and the postintervention time point (visit 5). The specific measures are categorized as follows (Table 1).

**Table 1 table1:** Summary of outcome measures.

Outcome domain			Instrument		Metric

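### With two assessments, a random intercept plus an autoregressive structure is over-parameterized and forces equal variances; the treatment effect stays estimable, but the covariance should be respecified

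*Protocol article*

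**What the plan says.** Under Outcomes (Overview), the protocol article fixes the schedule: "We will assess outcomes at baseline (visit 1) and the postintervention time point (visit 5". Table 1 and the outcome descriptions add no further occasion for either primary outcome.

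Under Statistical Methods, continuous outcomes are to be analysed with "linear mixed-effects models with random intercepts accounting for repeated measures and missing data". The fixed effects are treatment group, "time (modeled as a continuous variable), and the treatment-by-time interaction to estimate differential change between groups". The section then adds "An autoregressive covariance structure will be applied to account for temporal correlation". It names no other covariance structure and does not let the variance differ by visit.

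Two other places bear on the point. The Eligibility Criteria require a SNAP-IV inattention score of at least 12, and the change in that subscale is a primary outcome. The Sample Size section expects 30% attrition.

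**The concern.** With two visits there is one within-person correlation to model, and a random intercept already models it. An autoregressive term on top asks the data to divide that single correlation into two sources, which they cannot do. The analyst may then face a warning on the primary model, or variance components that merely reflect the optimizer's starting values.

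The second problem concerns the SNAP-IV outcome. A random intercept with a homogeneous autoregressive residual gives both visits the same variance. Selecting on a baseline score of 12 or more narrows the baseline distribution but not the later one. The model uses the ratio of covariance to baseline variance to let baseline inform missing post scores. If the common variance is wrong, so is that ratio, and this plan relies on the mixed model to deal with the missing data.

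**Working it through.** The plan's only planning figure, 98 participants, does not enter the identification argument. It serves below only as the size of the simulated trials.

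**1. Identification.** Let τ² be the intercept variance, σ² the residual variance and ρ the autoregressive correlation. The two-visit covariance has

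- variance V₁₁ = V₂₂ = τ² + σ²
- covariance V₁₂ = τ² + ρσ²

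That is two quantities for three parameters. For any chosen ρ, σ² = (V₁₁ − V₁₂)/(1 − ρ) and τ² = V₁₁ − σ² reproduce the same matrix. With V₁₁ = 1 and V₁₂ = 0.5 as an illustration:

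| ρ | σ² | τ² |
|---|---|---|
| −0.3 | 0.5/1.3 = 0.385 | 0.615 |
| 0 | 0.500 | 0.500 |
| 0.2 | 0.5/0.8 = 0.625 | 0.375 |
| 0.4 | 0.5/0.6 = 0.833 | 0.167 |

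The derivative matrix of the distinct covariance elements with respect to (τ², σ², ρ) has rank 2 at two visits. It has rank 3 at three or four visits.

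**2. What happens to the treatment effect.** One trial was simulated with 49 per arm, variance 10 at each visit, covariance 5.5, and each post score missing with probability 0.30 (the variances are assumptions). REML was run with ρ held fixed:

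| ρ | τ² | σ² | REML log-likelihood | Interaction | SE |
|---|---|---|---|---|---|
| 0 | 4.968 | 3.644 | −385.858588 | −1.48972 | 0.66384 |
| 0.3 | 3.407 | 5.206 | −385.858588 | −1.48972 | 0.66384 |
| 0.5 | 1.324 | 7.289 | −385.858588 | −1.48972 | 0.66384 |

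Every row has marginal variance 8.6127 and covariance 4.9684. The split is arbitrary; the interaction and its SE are not.

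**3. What software does.** The plan names RStudio. On another simulated data set of this design, R's nlme started at ρ = −0.3, 0, 0.2 and 0.4 returned ρ = −0.29, 0.00, 0.23 and 0.37, with intercept variance 4.86, 4.24, 3.44 and 2.59. The log-likelihood was −382.1034 each time. Over 100 data sets all fits converged, but variance-component intervals failed in 38. With glmmTMB, 14 of 30 fits gave warnings.

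**4. Equal variances.** Suppose the untruncated SNAP-IV score is normal with the same SD at both visits and correlation r. Put a = (12 − mean)/SD, λ = φ(a)/(1 − Φ(a)) and δ = λ(λ − a). As fractions of the untruncated variance, truncated baseline variance is 1 − δ and post variance is 1 − r²δ. Take mean 16, SD 4 and r = 0.6 (assumed):

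- a = −1, λ = 0.2876, δ = 0.2876 × 1.2876 = 0.3703
- baseline 0.6297; post 1 − 0.36 × 0.3703 = 0.8667; ratio 1.38
- true slope of post on baseline 0.60; covariance 0.60 × 0.6297 = 0.3778
- slope using the average variance: 0.3778/[(0.6297 + 0.8667)/2] = 0.505

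Over means 16 to 19, SDs 4 to 5 and r 0.5 to 0.6, the variance ratio runs from 1.13 to 1.56.

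With complete data this has no consequence. The common variance is estimated by the average of the two, so the variance of a change score is 2(V − V₁₂) = V₁₁ + V₂₂ − 2V₁₂, as in the unstructured model. With about 30% of post scores missing, two sets of simulations under assumed variances gave:

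| Scenario | Equal variance | Unstructured | ANCOVA |
|---|---|---|---|
| Arm-dependent dropout: mean SE (empirical SD) | 1.00 (1.06) | 1.02 (1.05) | 0.98 (not given) |
| Baseline-dependent dropout: mean SE | 0.944 | 0.987 | – |
| Baseline-dependent dropout: type I error, 300 runs | 4.7% | 4.0% | – |

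In the first scenario the equal-variance SE is 1.00/1.06 = 0.94 of the empirical SD, against 1.02/1.05 = 0.97 for unstructured. The equal-variance estimate also shifted by about 0.1 points. In the second, the two SEs differ by about 4%. With 300 runs the Monte Carlo error of a 5% rate is √(0.05 × 0.95/300) = 1.3 percentage points, so the two error rates cannot be told apart.

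**The case against.** The strongest defence is that nothing of inferential weight is lost. The target is a fixed effect, and step 2 shows that it and its SE are the same wherever the optimizer stops on the ridge. A reader might infer that the primary model cannot be estimated at all. The documents do not support that: only the division of the covariance is unidentified.

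A reader might also infer that the model will have to be replaced after the data are seen. Data Management and Safety Monitoring keeps the final dataset locked until the analysis plan is finalized, and the analyst works with coded groups, so there is still time to put this right.

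A third tempting reading is that continuous time imposes a linear effect of days on late attenders. That needs actual visit dates as the time variable, which the article does not state. With two visits coded 0 and 1, continuous time and a visit factor are the same model. A continuous-time autoregressive term on varying dates could even give weak formal identification, but the article does not specify that either.

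All of this stands, as does the observation that the equal-variance effect is small and vanishes with complete data. What remains is a stated structure that does not suit the stated schedule, and an equal-variance restriction that the entry rule makes doubtful for a primary outcome.

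**Conclusion.** The point holds as a modest specification error. The covariance model has one parameter more than two visits can support, so its variance components would be uninterpretable and warnings are likely in some software. This follows from the protocol alone and applies to every continuous outcome analysed this way. It does not threaten estimation of the treatment effect.

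The equal-variance restriction concerns SNAP-IV inattention. Its size rests on assumed means, SDs, correlations and dropout patterns: an SE about 4% to 6% too low, and a shift of about 0.1 points on a 0 to 27 scale when dropout depends on baseline differently by arm. It also assumes that the qualifying score is the visit 1 score. The article does not say so, and truncation would be weaker if eligibility was scored on a separate occasion.

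**What to change.** Delete the combination of random intercept and autoregressive structure. Then name one of these as the primary analysis:

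- visit as a two-level factor with an unstructured 2x2 within-person covariance, preferably with baseline means constrained equal across arms, as randomization justifies; or
- ANCOVA of the visit 5 score on the baseline score.

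The choice must be explicit, because they are not interchangeable. With free baseline means and complete data, the unstructured model estimates the difference in mean change. ANCOVA estimates a baseline-adjusted difference and is usually more precise: with equal variances, the ratio of its variance to that of the change analysis is (1 − r²)/[2(1 − r)] = (1 + r)/2, or 0.75 at an assumed r of 0.5. Dropping just one of the two redundant terms would cure the identification problem but keep the equal variances.

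The cost is a sentence or two in the analysis plan and no change to data collection. If the protocol text itself is amended, its own rule on ethics approval and registry update applies. The Results section reports no interim analyses and data collection until October 2026, so the change can be made before the dataset is unlocked.

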**Methods:**

This multisite, parallel-group, single-blind randomized clinical trial will recruit 98 adolescents aged 12 to 17 years with a confirmed diagnosis of ADHD according to the *Diagnostic and Statistical Manual of Mental Disorders, Fifth Edition*, from 2 outpatient centers in Brazil. Participants will be allocated 1:1 to an HIIT-based VR exergame intervention (Move Sapiens) or an active control condition using the same VR platform without vigorous physical exertion. The intervention comprises 20 sessions over 4 weeks delivered in a home-based format following supervised laboratory familiarization. Primary outcomes are Swanson, Nolan, and Pelham Rating Scale version IV inattention subscale scores and go/no-go commission errors. Secondary outcomes include working memory, cognitive flexibility, processing speed, impulsivity, sleep quality, and anxiety symptoms. Analyses will follow an intention-to-treat approach using linear mixed-effects models.

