Several limitations should be acknowledged. The single-blind design introduces the possibility of expectancy effects; however, this risk is partially mitigated by the use of an engaging active control condition matched for novelty and immersion. Notably, expectancy bias may disproportionately affect the parent-reported inattention outcome given that parents are aware of their children’s group assignment. The inclusion of the go/no-go task as a co–primary objective performance measure allows for a complementary assessment that is less susceptible to expectancy effects as it is independent of rater expectations. Furthermore, the 2 study arms differ not only in metabolic load but also in gross motor demand and task experience as the intervention requires full-body movement whereas the control condition involves joystick-only interaction. These differences are inherent to ecologically valid comparisons of this nature and preclude definitive attribution of any observed effects to a single component of the intervention. The 4-week intervention period may be insufficient to induce durable neuroplastic changes or sustained behavioral adaptations as longer intervention durations have been associated with stronger consolidation of executive function gains in meta-analytic studies. Nevertheless, budgetary and logistical constraints limited the feasibility of implementing longer protocols, and the selected intervention length is consistent with the duration most commonly used in studies evaluating HIIT, neuromodulation, and computerized cognitive training for ADHD [27]. Excluding participants currently receiving pharmacological treatment limits generalizability but was necessary to isolate the specific effects of the exercise intervention. Although parent-reported inattention outcomes may be subject to rater bias, this limitation is offset by the inclusion of objective, performance-based measures of inhibitory control, which have demonstrated sensitivity to high-intensity exercise interventions. Finally, while home-based delivery precludes direct supervision, structured remote monitoring provides systematic indexes of adherence and training intensity, thereby ensuring intervention fidelity.

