If the study demonstrates significant improvements in inhibitory control and inattention in the HIIT VR group compared with the nonexercise VR control, these findings will support the clinical efficacy of an HIIT-based VR exergame as a novel, engaging nonpharmacological intervention for adolescents with ADHD. Such results would have important implications for expanding treatment options in a population characterized by limited adherence to existing therapies. Conversely, if no differential effects are observed between groups, this would suggest that immersive VR engagement itself may represent a key therapeutic component, providing valuable insights for the design of future digital and game-based interventions. By evaluating a developmentally appropriate, home-based HIIT VR intervention within a rigorously controlled design, this trial has the potential to advance both the clinical and methodological evidence base for nonpharmacological treatments in ADHD. Results will be disseminated through peer-reviewed publications and scientific conferences regardless of the direction of the findings.

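### No rule says whether one or both primary outcomes must succeed: error is up to 9.75% if one suffices, and the stated 80% is not the trial's power if both are needed

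*Protocol article*

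**What the plan says.** The Abstract names two primary outcomes: "Primary outcomes are Swanson, Nolan, and Pelham Rating Scale version IV inattention subscale scores and go/no-go commission errors". Table 1 and the Primary Outcomes section repeat both, and Table 1 marks the inattention score as a parent report.

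Statistical Methods gives one threshold for all outcomes: "Statistical significance will be defined as a 2-sided" P value below .05. That section has no alpha split, no order of testing, and no statement of whether one or both primary outcomes must be significant.

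The Sample Size section uses one set of inputs: an effect of 0.50, power of 80% and "a significance level of an α value of .05". It does not say which primary outcome these belong to, or whether they refer to a joint result.

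The Discussion comes nearest to a success rule. It labels the go/no-go task co-primary, and its positive conclusion begins "If the study demonstrates significant improvements in inhibitory control and inattention in the HIIT VR group compared with the nonexercise VR control". The only other case it interprets is no difference between the groups. It also concedes that parents know the allocation and that "expectancy bias may disproportionately affect the parent-reported inattention outcome".

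**The concern.** With two primary outcomes there are three kinds of result: both significant, neither, or one of the two. The article interprets the first two and leaves the third open, while its only formal threshold lets each outcome be called significant at the full .05. The Methods therefore allow a claim on either outcome, and the Discussion suggests that both are needed.

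The gap has consequences in both directions. If either outcome may carry the claim, the chance of a false positive somewhere among the primary outcomes exceeds 5%. The claim could then rest on the parent rating alone, the outcome the article itself regards as most open to expectancy. The article treats the objective task as offsetting that weakness, but the task can guard the efficacy claim only if its result is needed for the claim. If both outcomes must succeed, the error is controlled, but the quoted power describes one test and not the trial.

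**Working it through.** **Inputs from the protocol article.** Two primary outcomes (Abstract, Table 1); two-sided .05 for each (Statistical Methods); power 0.80, alpha .05, effect 0.50, attrition 30%, 98 in total and 49 per arm (Sample Size). The correlation r between the two test statistics is not given. It is an assumption here, varied from 0 to 0.9.

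**The plan's own figure.** For a two-group comparison of means with d = 0.50, n per arm = 2(1.96 + 0.84)²/0.50², which rounds up to 63. That is 126 in total, and 126/0.70 = 180 after attrition. The stated 98 does not reproduce. It does match a within-arm paired calculation (34 per arm; 68/0.70 = 97.1, made even at 98). A between-group analysis would reach 34 per arm only with an unstated baseline correlation of about 0.68 (ANCOVA) or 0.73 (change score). This is a separate problem, kept apart below.

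**If either outcome suffices.** With both nulls true and independent tests, the family-wise error is 1 − 0.95² = 0.0975. For correlated tests it is 1 − P(|Z1| < 1.96, |Z2| < 1.96) under a bivariate normal:

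| Assumed r | Family-wise error |
|---|---|
| 0 | 9.75% |
| 0.3 | 9.5% |
| 0.5 | 9.1% |
| 0.7 | 8.4% |
| 0.9 | 7.0% |

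Counting only false positives that favour the intervention, the independent case gives 1 − 0.975² = 4.9%, against 2.5% for a single outcome. The near doubling is the same.

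**If both are required.** The error is at most 5%, and 0.05² = 0.25% if both nulls are true and the tests independent. Granting the stated 80% on each outcome, joint power is:

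- r = 0: 0.80² = 64%
- r = 0.3: 67%
- r = 0.5: 69%

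**How likely the undefined case is.** With 80% power on each outcome, the chance that exactly one is significant is 2 × (0.80 − joint power). That is 2 × (0.80 − 0.64) = 32% at r = 0, and 2 × (0.80 − 0.687) = 23% at r = 0.5. Even if the intervention works as assumed on both outcomes, a split result is a substantial possibility.

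**The case against.** Several points on the other side have weight.

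- **A reader might infer that the false positive rate is simply 9–10%.** The documents do not support that. The figure needs a rule that either outcome suffices, and no section says so. The co-primary label and the joint wording in the Discussion point towards requiring both, which keeps the error at or below 5%. A threshold for calling a P value significant is also not in itself a rule for declaring the trial positive. Even under an either-outcome rule, the figure falls below 9% once the correlation is much above 0.5.
- **A reader might compute joint power at 34 per arm and set it against 80%.** With d = 0.50 on each outcome and no baseline adjustment, the expected test statistic is 0.5 × √(34/2) = 2.06, giving joint power of 29% (r = 0) to 38% (r = 0.5). Most of that drop comes from the sample-size problem: power on a single outcome is already about 53% at that size. The joint rule itself accounts for the fall from 80% to 64–69%.
- **A reader might think that parental unblinding was overlooked or adds to the error rate.** It is disclosed as a limitation and forms no part of the 9.75%. A go/no-go result also helps in reading a parent-only win even where it is not required.
- **The rule may sit in the analysis plan.** That plan is not shown, and Data Management and Safety Monitoring keeps the dataset locked until it is finalized. This softens the point but does not remove it. The article does state a decision threshold, and that threshold does not settle what its own two primary outcomes and Discussion require.

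**Conclusion.** The point holds in conditional form. The Methods test both primary outcomes at two-sided .05 without a rule for a split result, and the Discussion leans towards needing both without making that a rule. Under an either-outcome rule the error is up to 9.75%, with the correlation assumed, and a claim could stand on the parent rating alone. Under a both-outcomes rule the error is at most 5%, but joint power is about 64% to 69% even if each outcome has the stated 80%. No reading delivers 5% error and 80% power together, short of perfectly correlated tests. That 98 does not reproduce for a two-group comparison is additional and is not counted in these figures.

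**What to change.** Before the dataset is unlocked, add to Statistical Methods, for example: *Superiority is claimed only if both primary outcomes favour the HIIT arm at two-sided P<.05; a significant result on one alone is reported as not confirming the hypothesis.* Restate power in Sample Size for that joint rule, giving the assumed effect for each outcome and the assumed correlation. This fits the Discussion, needs no alpha split, and makes the objective task a real safeguard against a parent-only win.

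If the sponsor prefers that either outcome may win, state that instead and use Holm: the smaller P value against .025 and, if it passes, the larger against .05. The Discussion should then say how a win on one outcome will be read.

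The choice is the sponsor's. The joint rule costs a lower stated power, and restoring 80% would need more participants. Holm costs a stricter first threshold. Either needs the ethics approval and registry update that the Ethical Considerations section requires for amendments. With 58 of 98 enrolled as of April 2026 and no interim analysis done, a rule fixed now would still be credible.
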